#### Analyses of Changes Over Time

We will present the proportions of patients experiencing the outcomes for each time period or mean changes for continuous variables and 95% CIs. Statistical significance of changes from pre to post time period will be assessed using the McNemar test for binary variables, the Wilcoxon signed rank test for original variables, and the paired *t* test for continuous variables. Regression models appropriate to outcome distributions will be used to control for potential confounders of age (<70 vs ≥70 years), sex, count of comorbidities (CPCSSN-validated conditions), neighborhood income quintile, and CPCSSN network (corresponding to location within Canada). Interactions will be examined in the descriptive analysis and will be considered for inclusion in models if they are found to be relevant. We will present adjusted estimates and 95% CIs for outcomes and parameter estimates for the independent variable and covariates. Analyses will be completed using SAS (version 9.4; SAS Institute, Inc).

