## Methods

### Data Source

The Canadian Primary Care Sentinel Surveillance Network (CPCSSN [40]) is a multidisease electronic medical record (EMR) research and surveillance data repository that securely collects deidentified health information from EMRs of participating primary care clinicians (eg, family physicians and nurse practitioners) who are referred to as “sentinels.” CPCSSN currently brings together 13 primary care research networks for the purposes of research, disease surveillance, and quality improvement, with more networks due to join in the near future. Every 6 months, CPCSSN acquires deidentified patient-level clinical data from primary care EMR systems held by 1583 primary care providers across Canada, with approximately 200 patient encounters per month per physician [20]. CPCSSN acquires most of the data fields in Canadian primary care EMRs with the exceptions of portable document format such as imaging data and the narrative “Subjective, Objective, Assessment, and Planning” notes. The acquired data are processed into a standard format and are made available for surveillance and research [41]. The relative frequency, longitudinal format, and comprehensiveness of CPCSSN data are ideal for the study of changes in practice, through time, in response to significant environmental imperatives, such as public health or research initiatives [41]. Numerous case definition validation studies have been completed [42-44], and the data have also been used to evaluate patterns and quality of health care [19,45].

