## Results

### Study Timeline

The start date of this study was October 5, 2022, and the prospective end date is January 31, 2024. At the time of writing (May 2023), we have finished data cleaning and begun exploratory analyses. As there are known consistencies with CPCSSN data, having a longer exploratory analysis phase has allowed us to liaise with central CPCSSN data managers in order to prepare data for the main analyses. We have now also defined our study cohort: a total of 875,934 individuals between the ages of 18 and 105 years as of 2018 were included.

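### The named pre-post tests treat patients as independent although they share providers; if the change varies between providers, p values are too small and matching CIs too narrow

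*Protocol article*

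**What the plan says.** Under Analyses of Changes Over Time, the article fixes the method for the pre-post comparison: "Statistical significance of changes from pre to post time period will be assessed using the McNemar test for binary variables". The Wilcoxon signed rank test is named for a second class of variable, and "the paired *t* test for continuous variables" completes the list. Proportions or mean changes are to be shown with 95% CIs.

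For the adjusted analysis it says: "Regression models appropriate to outcome distributions will be used to control for potential confounders of age", followed by sex, comorbidity count, income quintile and, last, "and CPCSSN network (corresponding to location within Canada". Network is the only grouping variable named. The covariance structure of these models is not stated.

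Under Data Source, the records come from "1583 primary care providers across Canada", and "CPCSSN currently brings together 13 primary care research networks". Under Study Timeline, "a total of 875,934 individuals between the ages of 18 and 105 years as of 2018 were included". Neither provider nor practice appears as a unit of clustering in the tests, the covariate list, the power statement, the sensitivity analysis or the limitations.

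**The concern.** Each of the three tests handles pairing within a patient and assumes that one patient's change tells nothing about another's. Many indicators in Table 1 (tests ordered, referrals, prescriptions, examinations) are decisions of the clinician or practice. If some providers cut back more than others, patients of one provider have correlated changes, and the tests understate the variance of the average change.

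The article itself gives reason to expect such variation. Its Introduction suggests that testing may have fallen towards more suitable levels in practices that had tended to overuse it, which is a change specific to some practices.

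The network covariate does not help. It is absent from the unadjusted tests. In a regression, a network main effect adjusts the level of the outcome across networks; it leaves the correlation of patients within the providers of a network untouched.

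At stake are the p values and intervals for many indicators, several of them in strata. Small changes could be reported as established when they lie within ordinary variation between providers.

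**Working it through.** **1. The plan's own sample size.** Inputs from Statistical Analysis and Power: 50% to 55%, within-pair correlation 0.2 or 0.1, stated sizes 1276 and 1432. Significance level and power are not stated; two-sided 0.05 and 80% are assumed.

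With p11 = p1·p2 + ρ·√(p1q1p2q2), discordance pd = p1 + p2 − 2·p11 and d = 0.05, the McNemar size is n = (1.96·√pd + 0.842·√(pd − d²))² / d².

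- ρ = 0.2: pd = 0.4005, n = 1255
- ρ = 0.1: pd = 0.4503, n = 1411

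Both are within 3% of the stated figures. Adding 1/d = 20 as a simple continuity correction gives 1275 and 1431. At 90% power the results are 1679 and 1888, which do not fit. The stated sizes are therefore those for independent patients, with no design effect.

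**2. Cluster sizes.** Whole cohort: m = 875,934 / 1583 = 553.3. With the article's prevalences, diabetes (10%) has 87,593 patients, m = 55.3; heart failure (4%) has 35,037, m = 22.1.

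**3. Design effect.** DE = 1 + (m − 1)·ICC, where ICC is the correlation of the within-patient change among patients of one provider, with equal cluster sizes. Intervals should be √DE times wider. For example, the whole cohort at ICC 0.01 gives 1 + 552.3 × 0.01 = 6.52, √6.52 = 2.55. The ICCs are assumptions.

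| ICC of change | Whole cohort: DE, CI factor | Diabetes: DE, CI factor | Heart failure: DE, CI factor |
|---|---|---|---|
| 0.001 | 1.55, 1.25 | 1.05, 1.03 | 1.02, 1.01 |
| 0.005 | 3.76, 1.94 | 1.27, 1.13 | 1.11, 1.05 |
| 0.01 | 6.52, 2.55 | 1.54, 1.24 | 1.21, 1.10 |
| 0.05 | 28.62, 5.35 | 3.72, 1.93 | 2.06, 1.43 |

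**4. False-positive rate.** A simulation with no average change used 1583 providers, 553 patients each, 40% discordant pairs and 1000 runs. ICC = SD² / 0.4.

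| SD of provider-level change (points) | ICC | McNemar rejections | Provider-level analysis |
|---|---|---|---|
| 0 | 0 | 4.5% | 4.2% |
| 2 | 0.001 | 11.1% | 5.0% |
| 5 | 0.006 | 35.5% | 3.9% |
| 10 | 0.025 | 61.4% | 5.2% |

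**5. Absolute width and sample size.** At 50% versus 55% with ρ = 0.2, the unclustered whole-cohort half-width is 1.96·√((0.4005 − 0.0025)/875,934) = 0.13 percentage points. It becomes 0.13 × 2.55 = 0.34 at ICC 0.01 and 0.71 at ICC 0.05. Effective sizes at ICC 0.05 are about 30,600 for the whole cohort, 87,593 / 3.72 ≈ 23,600 in diabetes and 35,037 / 2.06 ≈ 17,000 in heart failure. The larger stated requirement is 1432, so even heart failure exceeds it by a factor of about 12.

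**The case against.** Several objections have force.

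- **Adjusted models.** The article fixes only the three unadjusted tests. The regressions are described by outcome distribution alone, and an analysis plan not shown here may use GEE, random effects or a robust variance. This stands: a reader might infer that every interval in the study will be too narrow, but the article does not settle that for the adjusted estimates. It does not rescue the named tests, which such a plan would have to replace.
- **Common change.** A shift shared by all providers is the effect being estimated and adds no variance. This also stands: a pandemic-wide change is not in itself the problem. Only variation in the change between providers matters, and its size is unknown.
- **Size.** No ICC is given, 1583 is the total for the whole surveillance network and not a count for this cohort, and equal clusters are assumed. At ICC 0.001 the whole-cohort factor is only 1.25, and in the two exemplar conditions it is modest throughout. On the other side, for a given ICC, fewer contributing providers, unequal cluster sizes or clustering by practice would raise the factor.
- **Universal significance.** A reader might infer that clustering explains why nearly every indicator and subgroup contrast would reach significance. With 875,934 patients, that is mainly a matter of sample size; at ICC 0.05 a 1-point change would still be significant after correction. Nor do these design effects carry over to contrasts between groups seen by the same providers, such as age or sex, because a provider's shift common to both groups cancels. The article also warns, under Key Findings, that a decline may lack clinical importance.

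**Conclusion.** The point holds for the unadjusted tests. They assume independent patients, the patients are nested in providers and practices, and nothing stated in the article corrects for this. Whenever the change varies between providers, the p values are too small and the matching intervals too narrow.

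For the whole cohort the shortfall in width is about twofold from an ICC of 0.005 and about fivefold at 0.05. In diabetes and heart failure it is much smaller, so calling all intervals far too narrow would go beyond the documents. These sizes rest on the assumed ICCs, on all 1583 providers contributing and on equal cluster sizes.

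The consequence is overstated significance for small changes. No bias in the point estimates follows. A reader might also infer that the study is underpowered because its power statement has no design effect; the effective sizes above show that it is not. The change is worth making before the main analyses; at the time of writing they were still exploratory.

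**What to change.** In Analyses of Changes Over Time, state that tests and 95% CIs for the pre-post change use a variance clustered on provider or practice. Either of two forms would serve:

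- GEE with robust standard errors, with the provider or practice as the cluster and each patient's two records inside it. With an independence working correlation, the unadjusted estimate of change stays the same and only its standard error alters.
- A mixed model with a provider-level random effect for the change. A random intercept alone would not capture variation in the change.

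Apply the same clustering in the adjusted models and keep network as a covariate. Label any McNemar, Wilcoxon or paired t results as unclustered description. Report the number of contributing providers or practices.

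The cost is a few sentences of wording and slightly more analysis work with standard procedures in the SAS software already planned. Intervals will be wider.

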Early in the pandemic, there were reductions in visits for chronic condition management [20,26,27], preventive screening and diagnostic testing [28,29], and changes in physician referral behaviors [30]. The limited availability of testing and coordination of prevention services was a concern among Canadian family physicians [31]. Professional organizations recommended continuation of in-person care during the pandemic for complex chronic conditions and when physical examination was required; however, many patients avoided seeking primary care, and clinics experienced decreased attendance relating to the care of serious conditions [32,33]. Although telemedicine strategies can be effective for some chronic disease monitoring, patients who experience lack of equity in access to health care are also likely to experience barriers to using technology [34-36].

The onset of the pandemic worsened existing challenges to the prospects of achieving and maintaining an adequate level of comprehensive primary care in Canada. Understanding the ways in which the core functions of primary care [37-39] were affected by the COVID-19 pandemic is essential for chronic condition management and for system assessment overall. Although there are reports that the volume of primary care in Canada has largely returned to prepandemic levels, it is not clear whether and for whom there is a need to “catch up” on care for chronic diseases. For practices with a tendency for overuse of testing and investigations, these may have declined to more appropriate levels during the pandemic, also highlighting the areas of practice improvement. The objectives of this study are to describe the impacts of COVID-19 on chronic disease care and to determine whether changes were associated with patients’ sociodemographic characteristics and multimorbidity.

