#### Descriptive Analyses

To describe the cohort, continuous or count variables will be analyzed for their mean, median, SDs, and IQRs. For categorical variables, percentages will be calculated. We will present outcomes stratified by sex, age category (40-49, 50-59, 60-69, and ≥70 years), urban versus rural patient address, and neighborhood income quintile (1-2 [lower] vs 3-5 [higher]).

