#### Sensitivity Analysis

To examine whether results are biased because of the nonrepresentativeness of the CPCSSN population, we will conduct the analyses on a sample of patients that is representative of the Canadian population based on age, sex, neighborhood socioeconomic status, and rural or urban residence.

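### Urban/rural residence is a planned stratifier and balancing variable but is not on the regression covariate list, so no adjusted rural-urban estimate is prespecified

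*Protocol article*

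**What the plan says.** Three parts of the article's Methods bear on this.

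- Analyses of Changes Over Time gives the only list of regression covariates. The models will "control for potential confounders of age (<70 vs ≥70 years), sex, count of comorbidities (CPCSSN-validated conditions), neighborhood income quintile, and CPCSSN network". The section explains the last item as "CPCSSN network (corresponding to location within Canada". It then adds: "Interactions will be examined in the descriptive analysis and will be considered for inclusion in models if they are found to be relevant". On reporting, it says: "We will present adjusted estimates and 95% CIs for outcomes and parameter estimates for the independent variable and covariates".
- Descriptive Analyses stratifies outcomes by sex, age category, "urban versus rural patient address, and neighborhood income quintile (1-2 [lower] vs 3-5 [higher".
- Sensitivity Analysis repeats the analyses in a sample made "representative of the Canadian population based on age, sex, neighborhood socioeconomic status, and rural or urban residence".

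The Introduction gives the second objective as to "determine whether changes were associated with patients’ sociodemographic characteristics and multimorbidity".

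**The concern.** Descriptive Analyses and Sensitivity Analysis each name four patient characteristics. In both, residence is the only one of the four with no counterpart on the covariate list. The article gives a definite list, so this is not simply detail left to a fuller document.

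The second objective is at stake. It asks which patient characteristics go with changes in care, and the covariate estimates will be published and read as answers. Two consequences follow if the list stands:

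- A rural-urban difference would appear in the stratified tables without a planned adjusted counterpart.
- If rural and urban patients differ in income, age or comorbidity, and also in how their care changed, the adjusted estimates for those characteristics may pick up part of the rural-urban difference.

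**Working it through.** **1. The lists side by side.**

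| Characteristic | Stratifier | Sensitivity sample | Regression covariate |
|---|---|---|---|
| Age | yes | yes | yes |
| Sex | yes | yes | yes |
| Neighborhood income or socioeconomic status | yes | yes | yes |
| Urban/rural residence | yes | yes | no |
| Comorbidity count | no | no | yes |
| Network | no | no | yes |

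**2. Could another element fill the gap?**

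- *Network.* Data Source describes 13 networks across Canada. Network can absorb some geographic difference, but the article does not say that any network is wholly urban or wholly rural. It is a coarse proxy.
- *The interaction clause.* It could bring residence in, because residence is a descriptive stratum. The route depends on what the descriptive results show, and no residence main effect is listed.
- *The sensitivity analysis.* It changes who is in the sample. It neither adjusts for residence nor yields an adjusted rural-urban estimate.

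**3. Which estimates are exposed.** The design is a closed cohort with each patient compared with himself or herself. A characteristic that is largely fixed over time does not confound the overall pre-post change. Only the covariate estimates and the differences in change between patient groups are exposed.

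**4. The plan's own figure, as the source of a spread.** The article gives 1276 pairs for a change from 50% to 55% at correlation 0.2, and 1432 at correlation 0.1. It states neither alpha nor power; I assume two-sided 0.05 and 80%.

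- Discordant share: psi = p1(1-p2) + p2(1-p1) - 2 x rho x sqrt(p1 q1 p2 q2), where q = 1-p.
- At rho = 0.2: psi = 0.225 + 0.275 - 0.0995 = 0.4005.
- n = [1.96 x sqrt(psi) + 0.8416 x sqrt(psi - 0.05²)]² / 0.05² = 1255.03. Adding a continuity term of 1/0.05 = 20 gives 1275.03, which rounds up to 1276.
- At rho = 0.1: 1411.2 + 20 = 1431.2, which rounds up to 1432.

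Both figures reproduce, and nothing in this point alters them.

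**5. Possible size of the carry-over.** In a linear model, the shift in a low-versus-high income contrast is about (rural-urban difference in change) x (difference in rural share between the income groups, within network). The documents give neither input, so both are assumed.

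| Assumed rural-urban difference in change | Rural share differs by -20 points | 0 | +20 points |
|---|---|---|---|
| 2 points | -0.4 | 0 | +0.4 |
| 5 points | -1.0 | 0 | +1.0 |
| 10 points | -2.0 | 0 | +2.0 |

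**6. Set against sampling error.** The approximate 95% half-width for an income contrast with an assumed 40/60 split is 1.96 x SD x sqrt(1/(0.4N) + 1/(0.6N)). I take SD = sqrt(0.4005) = 0.633 from step 4 and ignore clustering.

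- Whole cohort, N = 875,934: 0.27 points.
- Diabetes at the article's 10% prevalence, N ≈ 87,593: 0.86 points.
- Heart failure at 4%, N ≈ 35,037: 1.35 points.

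A middle assumption of 5 points x 15% = 0.75 points exceeds the first half-width and falls below the other two.

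**The case against.** The strongest case against has four parts.

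- *Harm is not shown.* A shift needs residence to be related both to the characteristic and to the change, after network and the other covariates are accounted for. The documents give no figure for either relation. This stands, and it is why the point is worded as a possibility.
- *The target is association.* An income association that is not conditioned on residence is a legitimate descriptive quantity, and the abstract's example subgroups are age, comorbidities and socioeconomic status. This stands in part. Adding residence changes what the income estimate means. But residence is a sociodemographic characteristic that the plan itself chose to stratify by, so an adjusted estimate for it belongs to the second objective.
- *The sensitivity analysis is about external validity.* It addresses whether the database population represents Canada, and it does not name residence as a confounder. This stands: the sections do not contradict each other. They show only that the variable is held and considered relevant.
- *The adjusted differences in change are themselves loosely planned.* The article prespecifies no period interaction for income or age either. This stands, and it bears on the fix: in a model with a period term, a residence main effect alone would not adjust a difference in change.

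A reader might infer that residence is barred from every model and that the rural gap can only ever appear unadjusted. The interaction clause does not support that, because it leaves a conditional way in. What is missing is prespecification.

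**Conclusion.** The omission is real and is a modest defect that is cheap to repair. As prespecified, there is no adjusted rural-urban estimate, and the adjusted income, age and comorbidity associations may include rural-urban differences beyond those that network absorbs. The overall within-patient pre-post change is little affected.

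The sign and size cannot be determined from the article. The range of -2.0 to +2.0 points rests wholly on assumed inputs and includes zero.

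A reader might also infer, from the 0.27-point half-width in the whole cohort, that any such bias would swamp sampling error. The documents do not support that as a general statement. The comparison reverses in the diabetes and heart failure cohorts, to which many of the indicators belong. The spread is borrowed from an illustrative power scenario. Clustering of patients within the 1583 providers is ignored and would probably widen the intervals.

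**What to change.** In Analyses of Changes Over Time:

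- Add urban/rural residence to the covariate list for the regression models.
- Where differences in change between patient groups are estimated, also include the interaction of residence with period.
- Report the adjusted rural and urban pre-post changes next to those for income, age and comorbidity count.

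If the sponsor prefers to leave residence out, the text should say why network is considered sufficient.

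The cost is small: one variable that the plan already uses, one interaction term and a line of text. Some records without a usable address code will be lost or need handling, which should follow whatever is done for income quintile. The income estimates become conditional on residence, and the report should say so.

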**Objective:**

This study aims to describe the impacts of the COVID-19 pandemic on indicators of primary care access, comprehensiveness, and appropriateness among adult patients, as well as on specific indictors of chronic conditions. Additionally, this study aims to determine whether any identified changes were associated with patient sociodemographic characteristics and multimorbidity.

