### Variables of Interest

#### Primary Exposure

The primary exposure is the start of the pandemic in March 13, 2020. This date was selected as it marks the beginning of Canadian provincial governments responding to the formal declaration of the pandemic by the World Health Organization on March 11, 2020, by enforcing sweeping public health and safety measures. The prepandemic time frame used is defined as June 22, 2018, through March 12, 2020. The pandemic time frame used in this study runs from March 13, 2020, through December 31, 2022. In addition to comparison between these 2 periods, 30-day interval rates will also be calculated for selected outcomes and indicators where possible.

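### The second objective asks whose care changed, but the models treat patient characteristics as confounders and admit interactions only after a descriptive look

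*Protocol article*

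**What the plan says.** The Abstract (Objective) states that "this study aims to determine whether any identified changes were associated with patient sociodemographic characteristics and multimorbidity". The end of the Introduction repeats the aim: "to determine whether changes were associated with patients’ sociodemographic characteristics and multimorbidity". The Abstract's Conclusions also promise to identify patient characteristics that go with changes in care.

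The exposure is calendar period: "The primary exposure is the start of the pandemic in March 13, 2020" (Primary Exposure).

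Under Analyses of Changes Over Time, the characteristics enter as adjustment variables: "Regression models appropriate to outcome distributions will be used to control for potential confounders of age (<70 vs ≥70 years), sex, count of comorbidities", followed by neighborhood income quintile and network. The output is to be adjusted outcome estimates and "parameter estimates for the independent variable and covariates". On effect modification there is one sentence: "Interactions will be examined in the descriptive analysis and will be considered for inclusion in models if they are found to be relevant".

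Two other places bear on the objective. The Abstract's Methods promise to examine differences among subgroups by decade of age, number of comorbidities and socioeconomic status. Descriptive Analyses promises outcomes stratified by sex, age band, "urban versus rural patient address" and income group. That list contains no comorbidity stratum, and urban/rural residence is not among the model covariates.

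**The concern.** If the question is whether the change differs by group, the quantity to estimate is the period-by-characteristic interaction. A model with period and main effects assumes one common change on its scale, so it cannot answer the question. Its covariate coefficients say who receives more or less care over the two periods together. Reported as planned, they could be read as showing whose care changed.

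The interaction terms depend on an undefined judgement made on the same data. Terms kept because they looked large tend to be overstated, and their intervals ignore the selection. Terms not kept receive no estimate of a difference and no interval. That matters because the closing Conclusions hope to offer reassurance about older patients and those of lower socioeconomic status. Reassurance needs a small difference in change with a narrow interval, which is the result this rule would leave out.

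**Working it through.** **1. What a main-effects model returns.** Take a linear model for a proportion in two periods, with 40% of patients older (illustrative rates, not from the protocol, and all patients observed in both periods). The age coefficient is then the old-minus-young difference averaged over the two periods, and the period coefficient is the average change.

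| Case | Younger, pre to post | Older, pre to post | Period coefficient | Age coefficient | Difference in change |
|---|---|---|---|---|---|
| A: change differs | 50% to 50% | 50% to 40% | 0.6×0 + 0.4×(−10) = −4 points | (0 − 10)/2 = −5 points | −10 − 0 = −10 points |
| B: change is the same | 50% to 45% | 60% to 55% | −5 points | (10 + 10)/2 = +10 points | −5 − (−5) = 0 |

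Simulated data for 40,000 patients agree within sampling error. Case A gave period −0.039, age −0.045 and interaction −0.094. Case B gave period −0.046, age 0.099 and interaction 0.013. The age coefficient is large in B, where the change does not differ. In A it is half the true difference in change. Only the interaction separates the two cases.

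**2. The protocol's own sample size.** Statistical Analysis and Power gives 1276 pairs for 50% versus 55% at correlation 0.2, and 1432 at correlation 0.1. Alpha and power are not stated, so two-sided 0.05 and 80% are assumed. With p11 = p1p2 + ρ√(p1q1p2q2), discordance pd = p1 + p2 − 2p11 and d = 0.05:

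n = [1.960√pd + 0.842√(pd − d²)]² / d²

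- ρ = 0.2: pd = 0.4005, n = 1,255.0. Adding 1/d = 20 gives 1,275.03, rounded up to 1,276.
- ρ = 0.1: pd = 0.4503, n = 1,411.2. Adding 20 gives 1,431.2, rounded up to 1,432.

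Both figures reproduce. They concern the overall change only, not a difference in change between groups.

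**3. Is the interaction feasible?** For a 5-point difference in change between two groups, with share f in the group that changes, v1 = pd − d² (changing group) and v0 = pd with both proportions 50% (other group):

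N = (1.960 + 0.842)² × [v1/f + v0/(1 − f)] / 0.05²

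At ρ = 0.2, v1 = 0.398 and v0 = 0.400.

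| Split | ρ = 0.2 | ρ = 0.1 |
|---|---|---|
| 50:50 | 5,011 | 5,638 |
| 40:60 | 5,217 | 5,870 |
| 20:80 | 7,818 | 8,795 |

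Turned round at ρ = 0.2 and a 40:60 or 50:50 split, the detectable difference in change is about 0.4 points in all 875,934 patients (Study Timeline). It is about 1.2 points in some 87,600 patients with diabetes (10%) and about 1.9 points in some 35,000 with heart failure (4%), using the prevalences in Statistical Analysis and Power.

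**The case against.** **Stratified results are promised regardless.** A reader might infer that the equity question could go wholly unreported. The documents do not support that: outcomes by sex, age, residence and income are committed to without condition, and the Abstract adds subgroup differences by comorbidity count. What stands is narrower. These presentations are descriptive, no difference in change with an interval is named, and comorbidity count is absent from the strata in Descriptive Analyses.

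**The model form is open.** If within-person change were the outcome, covariate coefficients would be associations with change. But the article makes period the exposure and speaks of an independent variable and confounders, which fits a period model. It nowhere states a change score.

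**Adjustment has a purpose.** One might argue that a closed cohort balances fixed characteristics exactly across periods. It does not. Under Study Population, people who die contribute only until death, and entry rests on contact before the pandemic. Comorbidity count can also change. Adjustment is therefore reasonable, though it does not answer the second objective.

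**Scale matters.** A fall from 8 to 6 visits in older patients and from 3 to 2.25 in younger ones is the same as a ratio (6/8 = 2.25/3 = 0.75), although the age rate ratio is 8/3 = 2.67. In absolute terms the falls are 2 and 0.75 visits. Whether an interaction exists depends on the scale, which any remedy must state.

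**Selection bias is limited here.** It is tempting to say that any interaction kept would be badly inflated. At ρ = 0.2 and a 40:60 split, the standard error of a difference in change is about 0.14 points in the full cohort and 0.7 in heart failure. A true 5-point difference lies at least 7 standard errors from zero (5/0.7) and would hardly be inflated. The problem bites for small effects. Nor can a count of chance findings be held against the present rule alone: prespecifying many interactions raises the same multiplicity.

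**Conclusion.** The point holds in a limited form. The protocol states an objective about differences in change but commits to no estimate of one. Its reported covariate coefficients describe level of care, and the interaction terms depend on an undefined, data-driven judgement. An analysis plan could add detail, but the conditional rule is stated in the article itself.

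The overall pre-post estimates for the first objective are not affected, and the descriptive strata give a partial answer to the second. The documents do not show that the authors intend to present level differences as differences in change, only that the plan as written allows it. The feasibility figures rest on assumed two-sided 5% and 80% power, a 5-point difference, correlations of 0.1 to 0.2 and the stated prevalences. Even the largest requirement, 8,795 patients, is well below the roughly 35,000 expected with heart failure.

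**What to change.** In Analyses of Changes Over Time, for a named set of key indicators:

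- Prespecify period-by-characteristic terms for age, sex, comorbidity count, income quintile and urban/rural residence as the analysis for the second objective.
- Use a model that accounts for repeated measures within patient and for person-time, since death shortens follow-up and the two periods under Primary Exposure differ in length.
- State the scale of change, ratio or absolute, for each type of outcome.
- Report the adjusted change within each level and the difference in change with 95% CI, whatever the descriptive analysis shows. Delete the condition that an interaction must first look relevant.
- Interpret the many contrasts by size and interval, or state a multiplicity approach.

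Add comorbidity count to the strata in Descriptive Analyses and align the age categories, which are by decade in the Abstract and split at 70 in the models. The cost is protocol wording, more model terms and a longer set of results. No further data are needed beyond the variables already planned.
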